**Figure 1 figure1:**
[figure not shown]
A sample text message for assessing depression and its related conditions. The asterisks highlight the important part of the message.

**Figure 2 figure2:**
[figure not shown]
Randomization and data collection plan. DCAT: Diabetes-Depression Care-management Adoption Trial; GAD-2: 2-item Generalized Anxiety Disorder scale; INTW: interviewer; PHQ-8: 8-item Patient Health Questionnaire; SDS: 3-item Sheehan Disability Scale; SMS: short message service.

### Patient Safety Plan

If patients report a PHQ-8 score of 8 or higher in any one of the assessments, at the end of the assessment week, a text message will be sent to suggest that they speak to their clinician. Although the chance is small, participants may express thoughts about being better off dead, hurting him/herself, or other suicidal ideation at some point during the telephone recruitment or interview. If this occurs, the recruiter or interviewer will say, “I am not a clinician and I am not qualified to evaluate these thoughts and feelings in detail, but it is important that you get proper medical attention and I would encourage you to discuss these thoughts and feelings with a medical or mental health professional.”

### Statistical Analysis

Concordance between SMS text message and interview assessments will be measured by the intraclass correlation coefficient (ICC) and the kappa statistic. ICC measures the consistency or reproducibility of SMS text message and INTW assessments. We will calculate both the consistency and absolute agreement measures of ICC. The kappa statistic measures interrater agreement for categorical items. We will use different threshold levels to compute kappa, including PHQ-2 ≥3 and PHQ-8 ≥8, two threshold levels that were suggested to classify major depression [22,28]. We will also compute paired *t* tests to investigate differences in mean scores between SMS text message and interviewer assessments. ICC and kappa will be computed using the “icc” and “kappa2” functions in the R package “irr” (The R Foundation). Paired *t* tests will be performed by the R function “t.test.” Test-retest reliability of the SMS text message and interviewer assessments will also be measured by ICC. Finally, internal consistency will be measured by Cronbach alpha, which will be computed using the “alpha” function in the R package “psych.”

Since information such as depression and functional disability is sensitive health information, it is critical to understand whether participants are willing to self-disclose such information in an SMS text message assessment. We will calculate the proportion of missing data and explore whether the data are missing at random or is likely to follow some patterns, using descriptive and visualization tools provided by the R packages “mice” and “VIM.” We will also perform multiple imputation on the data and compare the concordance and reliability measures on original and imputed data [47].

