**Methods:**

The proposed study will adopt a randomized design with 200 patients assigned to four study groups: SMS/INTW, INTW/SMS, SMS/SMS, and INTW/INTW. The first two groups will be used to examine the concordance between SMS text message and interviewer assessments. The third and fourth groups will be used to evaluate test-retest reliability. Participants of the study will be recruited from the participants of the prior Diabetes-Depression Care-management Adoption Trial, a large comparative effectiveness research trial in collaboration with the Los Angeles County Department of Health Services. Test-retest reliability and concordance between SMS text message and interviewer assessments will be evaluated by the interclass correlation coefficient and the kappa statistic. Missing data patterns will be explored to understand whether participants are willing to self-disclose information related to depression in SMS text message assessments.

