### Recruitment

Participants of this study will be recruited from the group of participants from the prior Diabetes-Depression Care-management Adoption Trial (DCAT), a large, US Department of Health and Human Services-funded translational study conducted from 2010 to 2013 [15,31-37]. These patients will be chosen from the DCAT because of the prior contacts and rapport built during the DCAT so that this study can fit within the short timeline of the funding requirements. The DCAT was a comparative effectiveness research trial with three study arms in collaboration with eight safety-net primary care clinics of the Los Angeles County Department of Health Services, the second-largest safety-net system in the United States. The DCAT tested an automatic telephone depression-monitoring system to facilitate collaborative depression care in patients with type 2 diabetes. A bilingual recruiter and interviewer from the DCAT will join the proposed study and will contact the participants in the DCAT technology-facilitated care (TC) group for recruitment. Participants in the DCAT TC group received regular depression monitoring every 3 or 6 months over automatic telephone calls during the DCAT. For those who agree to participate, a random number generator will be used to randomize the patients into one of the four study groups. Participants assigned to the INTW/SMS and INTW/INTW groups will receive assessments over the telephone immediately after they agree to participate. Participants assigned to the SMS/INTW and SMS/SMS groups will be notified that an SMS text message assessment will be sent to them within 48 hours.

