## Discussion

This paper proposed a study with a randomized design to analyze SMS text message assessment, in both English and Spanish, for depression and its related conditions in a safety-net primary care population. The US Preventive Services Task Force recommends depression screening for all adults but does not mention the mode of screening [13]. Existing research has tested the PHQ for depression screening using paper-based self-reported assessment [48-50], in-person interviewer assessment [25,51], and telephone interviewer assessment [15,25]. To the best of our knowledge, there is no published paper about how widely each of those assessment modes are used in practice. The DCAT study was conducted in the Los Angeles County Department of Health Services, which carries out depression screening using the PHQ by in-person interviewer assessment. Compared to other assessment modes, SMS text message assessment is inexpensive, private, and scalable in large populations. Such advantages of SMS text message assessment are particularly beneficial for our targeted population in this study (ie, low-income, racially and ethnically diverse, safety-net patients with diabetes). These patients often face more significant individual and systemic barriers to receive timely depression assessment and treatment. Thus, the proposed SMS text message approach, if successful, could be a beneficial addition to primary care for these patients by providing proactive and timely depression assessment.

The proposed study will generate data and results that fill in the gap of current evidence in technology-mediated assessment for sensitive health information such as depressive symptoms. Current evidence on the effect of technology on self-disclosing such information is inconsistent. Some studies suggest that technology-mediated assessment such as SMS text messaging can create an idealized perception of the interviewer and reduce social desirability bias [52]. As a result, technology-mediated assessment can encourage disclosure of sensitive health information [53,54]. In contrast, there is also evidence suggesting technology-mediated assessment discourages disclosure of sensitive information, since the distance and private space created by technology may discourage patients to seek help [55].

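### Willingness to disclose by SMS is inferred from the amount and pattern of missing data, with no stated contrast against the randomised interviewer mode

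*Protocol article*

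**What the plan says.** The protocol article's Statistical Analysis section gives disclosure its own paragraph. It states that "it is critical to understand whether participants are willing to self-disclose such information in an SMS text message assessment". The method follows: "We will calculate the proportion of missing data and explore whether the data are missing at random or is likely to follow some patterns". The tools named for this step, the R packages mice and VIM, are there to summarise and plot; no test or estimate is attached to them. The Methods paragraph of the Abstract makes the same link: "Missing data patterns will be explored to understand whether participants are willing to self-disclose information related to depression in SMS text message assessments".

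Two other planned analyses come near the question without being assigned to it:

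- **Multiple imputation**, which serves concordance and reliability: "We will also perform multiple imputation on the data and compare the concordance and reliability measures on original and imputed data".
- **Paired t tests**, listed under concordance: "paired *t* tests to investigate differences in mean scores between SMS text message and interviewer assessments".

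The rationale is comparative. The Abstract's Background describes conflicting evidence on technology versus interviewer assessment of sensitive information. The Discussion repeats it ("Current evidence on the effect of technology on self-disclosing such information is inconsistent"), sets out both possible directions, and says the study will help close that gap.

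On timing, the Recruitment section says: "Participants assigned to the INTW/SMS and INTW/INTW groups will receive assessments over the telephone immediately after they agree to participate". Participants whose first assessment is by SMS are told to expect it within 48 hours. Under Randomization and Data Collection Plan, the second assessment falls within a 7-day period in all four groups.

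**The concern.** The rationale asks whether people disclose more or less by text than to an interviewer. The stated method describes missing data and names no reference value. If, say, 15% of SMS items were missing, that figure alone could not show whether SMS had discouraged disclosure, because the interviewer figure might be 5% or 25%.

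Two further limits follow from relying on missing data:

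- It cannot detect people who answer but under-report. That is the social-desirability mechanism that the Discussion itself describes.
- The text does not say whether *Don't know* and *Refuse to answer* count as missing, or whether they are kept apart from a text that was never answered. These are different behaviours, and only an explicit refusal is plainly about disclosure.

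At stake is a disclosure conclusion drawn without a control in a trial that randomised one.

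**Working it through.** **Inputs.** Enrolled numbers come from the Results section: SMS/INTW 52, SMS/SMS 53, INTW/SMS 49, INTW/INTW 52. The sum 52 + 53 + 49 + 52 = 206 matches the reported total. The planned size, 4 × 50 = 200, rests on precedent and funding, so there is no power figure to reproduce. The article gives no expected non-response rate and no alpha. The rates below and the two-sided 0.05 level are my assumptions.

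**Step 1: which comparisons randomisation supplies.**

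- First assessment: SMS 52 + 53 = 105; interviewer 49 + 52 = 101.
- Second assessment: SMS 53 + 49 = 102; interviewer 52 + 52 = 104. Within SMS-first this is 53 vs 52, and within INTW-first 49 vs 52.

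**Step 2: which of them suits non-reply.** The first interview follows agreement directly, on the telephone, so it should be nearly complete whatever the effect of mode. The first SMS arrives later. A first-assessment completion contrast therefore mixes mode with timing. At the second assessment both modes are delayed within the 7-day period, mode is randomised within each first mode, and every randomised participant can stay in the denominator.

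**Step 3: precision of the second-assessment contrast.** The half-width is 1.96 × √[p₁(1−p₁)/104 + p₂(1−p₂)/102], and power uses the pooled-variance two-proportion test.

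| Assumed non-completion, INTW vs SMS | 95% CI half-width (points) | Power |
|---|---|---|
| 5% vs 10% | 7.2 | 28% |
| 5% vs 15% | 8.1 | 67% |
| 5% vs 20% | 8.8 | 91% |
| 10% vs 20% | 9.7 | 52% |
| 10% vs 25% | 10.2 | 81% |

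For the last row, 1.96 × √(0.09/104 + 0.1875/102) = 0.102. The arcsine method gives 83% power there. Combining the two strata with Mantel-Haenszel weights leaves the half-widths unchanged to this precision.

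**Step 4: the SMS proportion alone.** With n = 105, the half-width 1.96 × √[p(1−p)/105] is 4.2 points at p = 5% and 8.8 points at p = 30%. A proportion can be estimated this well and still say nothing about direction without a reference.

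**Step 5: mean scores.**

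- First assessment, 105 vs 101, 80% power: (1.96 + 0.84) × √(1/105 + 1/101) = 0.39 SD.
- Planned paired t test, crossed groups, at most 52 + 49 = 101 pairs: 2.80 × √[2(1−r)/101] = 0.28 SD at an assumed within-person correlation r = 0.5, and 0.18 SD at r = 0.8.

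Both figures assume full completion. The paired test is the more sensitive of the two for score levels, but it drops anyone without both scores and so cannot speak to non-reply or refusal.

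**Step 6: where refusal can be seen.** In Table 1, *Refuse to answer* is offered only on the ten GAD-2 and PHQ-8 items. Pain items 14 and 15 offer only *Don't know*; the three SDS items and item 16 offer neither.

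**The case against.** The strongest reply is that the plan does more than count missing values, and promises less than a comparative answer.

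- It explores patterns as well as the proportion. This is right: a reader might infer that the missing proportion is the only evidence, but the text does not support that.
- It does compare the modes, through the paired t tests. A reader might infer that the interviewer comparator is never used. That is too strong: a shift in mean score bears on disclosure. What remains is that the tests are not linked to the disclosure question and are blind to non-responders.
- Disclosure is not a main purpose. A reader might take it for one of two stated aims, but the Objective names concordance and test-retest reliability, and the Discussion describes the disclosure output as preliminary and words it for SMS. This stands and limits the weight of the point.
- The missing-data sentence is not confined to SMS, and an analysis plan not shown might tabulate by mode. That is possible. However, the article fixes a method for this question, down to the R packages, and the method contains no contrast.
- The remedy is imperfect. Second-assessment completion measures willingness to reply, not disclosure itself; a telephone call and a text differ in effort; and within each stratum mode is tied to repeating or switching mode. First-assessment refusal rates and means exist only for responders. A reader might infer that an unbiased randomised answer on disclosure is already in the data. Only second-assessment completion is a fully randomised comparison.

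**Conclusion.** The point holds in a limited form. The article ties willingness to disclose to the amount and pattern of missing data and states no contrast with the interviewer mode for it, although the rationale is comparative and mode was randomised. As fixed, the method cannot show whether SMS raises or lowers disclosure.

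The available comparison is modest. Second-assessment completion (102 vs 104) gives a CI half-width of about 7 to 10 points at the assumed rates. Power reaches about 80% to 90% for differences of 15 points from a 5% to 10% base, and is low for differences of 5 to 10 points (28% to 67%). It should therefore be read as an estimate with an interval. All rates are assumptions. This is a worthwhile, inexpensive improvement to a secondary output and does not touch the concordance or reliability aims.

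**What to change.** Add the following to the Statistical Analysis section:

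1. Report non-reply, *Don't know* and *Refuse to answer* separately, by mode.
2. Compare completion of the second assessment, SMS vs interviewer, among all randomised participants, stratified by first mode (SMS/SMS 53 vs SMS/INTW 52; INTW/SMS 49 vs INTW/INTW 52), as a risk difference with 95% CI. Interpret it as willingness to reply. Do not make this contrast at the first assessment, where timing differs by mode.
3. At the first assessment, report by mode, with CIs, the *Don't know* and *Refuse to answer* rates for the GAD-2 and PHQ-8 items and mean PHQ-8, GAD-2 and SDS scores. Label these as conditional on response, with multiple imputation of the scores as a sensitivity analysis. Read them together with the planned paired t tests when drawing the conclusion on disclosure.
4. Keep the mice and VIM displays as description.

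The cost is a little more analysis of data already collected. The drawback is that small differences will be estimated imprecisely, which the report should say.

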## Discussion

This paper proposed a study with a randomized design to analyze SMS text message assessment, in both English and Spanish, for depression and its related conditions in a safety-net primary care population. The US Preventive Services Task Force recommends depression screening for all adults but does not mention the mode of screening [13]. Existing research has tested the PHQ for depression screening using paper-based self-reported assessment [48-50], in-person interviewer assessment [25,51], and telephone interviewer assessment [15,25]. To the best of our knowledge, there is no published paper about how widely each of those assessment modes are used in practice. The DCAT study was conducted in the Los Angeles County Department of Health Services, which carries out depression screening using the PHQ by in-person interviewer assessment. Compared to other assessment modes, SMS text message assessment is inexpensive, private, and scalable in large populations. Such advantages of SMS text message assessment are particularly beneficial for our targeted population in this study (ie, low-income, racially and ethnically diverse, safety-net patients with diabetes). These patients often face more significant individual and systemic barriers to receive timely depression assessment and treatment. Thus, the proposed SMS text message approach, if successful, could be a beneficial addition to primary care for these patients by providing proactive and timely depression assessment.

The proposed study will generate data and results that fill in the gap of current evidence in technology-mediated assessment for sensitive health information such as depressive symptoms. Current evidence on the effect of technology on self-disclosing such information is inconsistent. Some studies suggest that technology-mediated assessment such as SMS text messaging can create an idealized perception of the interviewer and reduce social desirability bias [52]. As a result, technology-mediated assessment can encourage disclosure of sensitive health information [53,54]. In contrast, there is also evidence suggesting technology-mediated assessment discourages disclosure of sensitive information, since the distance and private space created by technology may discourage patients to seek help [55].

The proposed study has a few limitations. First, the sample size is relatively small due to the limit of our funding. Second, the study participants’ experience built in the prior DCAT study may make those participants more familiar with technology-mediated assessment than average people in the targeted study population. Nevertheless, the 4-year interval between the DCAT study, conducted from 2010 to 2013, and this study, conducted in 2017, is long enough that it is likely to decrease the potential influences of DCAT assessment. Finally, the study participants are predominantly Latino, which may limit the generalizability of the study results to other safety-net primary care populations, especially those with a majority of African American patients.

The anticipated outcome of this study is to establish feasibility of using SMS text messaging to assess depression and its related conditions. Specifically, we aim to gather data and results for concordance and test-retest reliability of SMS text message and interviewer assessments in low-income, racially and ethnically diverse populations with diabetes. We also expect to generate preliminary knowledge about whether patients in the targeted population will be willing to reply and self-disclose sensitive health information about depression and its related conditions through SMS text message assessments.

## Abbreviations

DAS: 9-item Dysfunctional Attitudes Scale
DCAT: Diabetes-Depression Care-management Adoption Trial
DSS: Depression Stigma Scale
GAD-2: 2-item Generalized Anxiety Disorder scale
ICC: intraclass correlation coefficient
INTW: interviewer
PHQ: Patient Health Questionnaire
PHQ-2: 2-item Patient Health Questionnaire
PHQ-8: 8-item Patient Health Questionnaire
SDS: 3-item Sheehan Disability Scale
SMS: short message service
TC: technology-facilitated care
TIPI: Ten Item Personality Measure
